## Abstract

**Background:**

The prevalence of amphetamine-type stimulant use is greater than that of opioids and cocaine combined. Currently, there are no approved pharmacotherapy treatments for amphetamine-type stimulant problems, but some face-to-face psychotherapies are of demonstrated effectiveness. However, most treatment services focus on alcohol or opioid disorders, have limited reach and may not appeal to users of amphetamine-type stimulants. Internet interventions have proven to be effective for some substance use problems but none has specifically targeted users of amphetamine-type stimulants.

**Design/method:**

The study will use a randomized controlled trial design to evaluate the effect of an internet intervention for amphetamine-type stimulant problems compared with a waitlist control group. The primary outcome will be assessed as amphetamine-type stimulant use (baseline, 3 and 6 months). Other outcomes measures will include ‘readiness to change’, quality of life, psychological distress (K-10 score), days out of role, poly-drug use, help-seeking intention and help-seeking behavior. The intervention consists of three modules requiring an estimated total completion time of 90 minutes. The content of the modules was adapted from face-to-face clinical techniques based on cognitive behavior therapy and motivation enhancement. The target sample is 160 men and women aged 18 and over who have used amphetamine-type stimulants in the last 3 months.

**Discussion:**

To our knowledge this will be the first randomized controlled trial of an internet intervention specifically developed for users of amphetamine-type stimulants. If successful, the intervention will offer greater reach than conventional therapies and may engage clients who do not generally seek treatment from existing service providers.

**Trial registration:**

Australian and New Zealand Clinical Trials Registry (www.anzctr.org.au/) ACTRN12611000947909

## Background

Amphetamine-type stimulants (ATS) include an array of psychoactive substances, the most commonly used illicit ATS being methamphetamine, amphetamine and ecstasy (3,4-Methylenedioxymethamphetamine) [1,2]. There are now an estimated 35 million ATS users worldwide compared with combined total of 29 million opioid and cocaine consumers [3,4]. The age of initiation of ATS is typically in the mid-late teens, with levels of use often peaking in early adulthood. In Australia, the lifetime prevalence of use is highest among those aged 20-29 years (ecstasy 25%, meth/amphetamine 15%), with the respective 12-month figures being 10% and 6% among the same age group [5].

While the bulk of ATS use is recreational in nature, this population includes a sizable proportion of people who become dependent and experience chronic debilitating health problems as a result of their use of ATS [6]. Major health concerns include paranoia, aggression, increased risk of stroke and cardiovascular pathology [7]. Dependence on ATS, like dependence on any drug, is typically associated with a reduction in quality of life, premature mortality and elevated levels of crime [8]. This is particularly the case with the use of more potent ATS, such as crystalline methamphetamine, and with more efficient routes of administration (e.g., smoking or injecting) [9]. Reducing the impact of ATS use requires the simultaneous development of effective management strategies and methods to improve the uptake and accessibility of treatments for this population. The spectrum of ATS use will also need to be considered, from irregular use through to stimulant use disorders (abuse, dependence) [10].

Despite the widespread use of ATS, a systematic review concluded that, to date, there are insufficient data to support the use of pharmacotherapies such as fluoxetine, amlodipine, imipramine and desipramine in the treatment of amphetamine abuse and dependence [11]. However, research continues to assess other potential agents in the treatment of stimulant abuse [12,13]. A review of psychosocial treatments for methamphetamine dependence reported that the intensive application of psychological interventions (e.g., contingency management, cognitive behavior therapy (CBT), motivational interviewing) can result in a moderate reduction in stimulant use [14]. Brief cognitive behavioral interventions, of up to four sessions duration, have also been shown in previous research to be associated with significant reductions in amphetamine use and significantly greater likelihood of abstinence than controls [15]. However, these types of structured psychological interventions are not widely implemented in community-based treatments for drug use, and ATS users seeking help from traditional drug and alcohol services frequently report their needs are not being met [10]. For example, among a sample of methamphetamine users in Queensland, Australia, the majority felt that more information about methamphetamine use should be available and more accessible outside treatment services and business hours [16]. In particular, respondents reported that needle and syringe programs, methadone maintenance programs and outpatient counseling should not be co-located, as doing so is viewed as a key barrier to treatment access. The need to develop appropriate, novel treatments that are well accepted by ATS communities is clear, including options for accessing treatments outside mainstream specialist treatment services [17].

Given that psychological treatments can reduce stimulant use [15,18], there is the potential to develop internet-based treatments for ATS users, with many internet-based CBT treatment packages currently accessible via the world wide web [19]. The critical advantage offered by web-based interventions for mental health and substance use problems is that they have the potential to greatly reduce key barriers to obtaining treatment, in particular, stigma (given the anonymous access), cost (with free treatment), reach (potentially worldwide coverage and 24 hour access), especially for those living outside of metropolitan areas [20,21]. This is important in the context of ATS use, not only because of the number of people potentially requiring treatment but because surveys show that stimulant users are reluctant to seek treatment from existing drug treatment services as most are tailored toward clients with opiate or alcohol problems [1,22]. Furthermore, for those with addictive disorders, access to treatment ‘24/7’ may be a particularly important benefit of internet services, allowing the potential to capitalize on times of high motivation to change behavior and access to resources when the risk of relapse is high.

Internet-based interventions have already been demonstrated as effective for the treatment of depression and a range of anxiety disorders [23]. With respect to substance use, web-interventions have been effective in reducing problematic use of alcohol in young adults [24] and in reducing cannabis use via school-based interventions that involve on-line materials [25]. Brief internet interventions have been shown to reduce drug use and ‘high-risk’ behavior in human immunodeficiency virus (HIV) positive drug users [26] and a computerized intervention using combined CBT and motivational interviewing (MI) has been reported to reduce cannabis and alcohol use among those with co-morbid major depression [27]. However, the current authors are not aware of any evaluated internet based interventions for the use of ATS.

The objective of the study was to adapt existing face-to-face psychological approaches (i.e., CBT and MI) for delivery via the internet to reduce the use of ATS and associated problems plus improve motivation to reduce ATS use, with assessment of effectiveness at 3 and 6 months post-intervention.

## Method

### Design

A two-group randomized controlled trial will be used. The intervention group will receive an internet intervention consisting of three modules (detailed below). The wait-list control group will undertake the same assessments as the intervention group, with access to the intervention site at 6 months post enrolment. In addition, all participants will be provided with contact details for emergency services.

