### Procedure

Enrolment and screening will be undertaken via the internet. Advertisements will direct participants to the study web address. First, participants who visit the study website will be given information on the project and their eligibility assessed by means of a series of online questions. Based on their answers, participants who are not eligible for the study will be given information about other potentially useful websites and resources (e.g. mental health, alcohol or other drugs websites and helplines). Participants who are eligible for inclusion will be asked to provide active consent by ‘clicking’ on a box for each element of the consent form in order to enroll in the study. Figure1 illustrates the flow of participants through the study. Participants will be asked to provide an e-mail address that will be verified via a personalized link in an automated email. This link will take participants to the study site where they will set their own username and password. Participants will then be directed to an online baseline survey before being randomized to study groups. The randomization process will be fully automated with permuted blocks of four and will be implemented within the program.

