**Figure 1 F1:**
[figure not shown]
Participant flow through the study.

Participants who are assigned to the intervention group will then be provided with immediate access to the first module of the intervention. These participants will be advised to allow 1 week between modules, but are allowed to proceed at their own pace. Participants must visit each page of a module in sequence to complete the module and thus obtain access to the next one. The intervention group will receive emails at seven day intervals after the commencement of the trial period, either asking them to start the next module, if they have not already commenced that module, or inviting them to revisit the site. A further e-mail will be sent to those who do not start the current module at 3 days after the module was scheduled for commencement. Participants will be invited via e-mail to complete follow-up assessment at 3 and 6 months (91 and 183 days) post-randomization with a further two reminder emails at 7 day intervals if required, followed by a telephone call(s) for participants who do not respond to the emails. Participants will receive AU$20 for baseline assessment and for each follow-up questionnaire that they complete, paid as either on-line vouchers or posted cheques.

The Australian National University Human Research Ethics committee approved the study, which is also registered with the Australian and New Zealand Clinical Trials Registry (www.anzctr.org.au/) ACTRN12611000947909.

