### Measures

Both the primary and secondary outcome measures will be assessed at baseline, 3 and 6 month. The primary outcome measure will be ATS use, assessed using the World Health Organization Alcohol, Smoking, Substance Involvement Screening Test (ASSIST) [28,29]. The ASSIST first assesses lifetime use of nine categories of drugs (i.e. tobacco, alcohol, cannabis, cocaine, ATS, inhalants, sedatives, hallucinogens, opioids and other). Then, for any drug identified by the lifetime question, data relating to the last 3 months is collected on: frequency of use, cravings, problems (health, social legal or financial), and failure to fulfill roles. Next, the ASSIST ascertains if a friend or relative has ever expressed concern about their drug use and if the person has ever tried and failed to control their drug use. Finally, injection of drugs is assessed. The standard ASSIST scoring algorithm will be used to generate a score related to use of ATS [28].

The secondary outcomes will be: (a) health-seeking intention and help-seeking behavior measured with the general help-seeking questionnaire (GHSQ) [30] and the actual help-seeking questionnaire (AHSQ) [31,32]; (b) readiness to change assessed using a modified version of the Readiness to Change Questionnaire (RTCQ) [33] referencing ATS rather than alcohol; (c) psychological distress assessed using the Kessler 10 [34]; (d) poly-drug use measured by the ASSIST [28]; (e) days out of role [35]; and (f) quality of life assessed by the European Health Interview Survey (EUROHIS) Quality of Life scale [36]. The baseline measures include demographic information (e.g., age, sex, marital status), drug use history (age of first use of ATS), and severity of dependence assessed using the Severity of Dependence Scale [37].

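### Control access to the intervention is set by calendar at 6 months, while the 6-month survey is still being collected, so late-responding controls can have the site open before they report the outcome

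*Protocol article*

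**What the plan says.** Three parts of the Protocol article bear on this point.

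- **Design** sets the control arm's assessments: "The wait-list control group will undertake the same assessments as the intervention group". The same sentence then fixes when the modules become available to these participants: "with access to the intervention site at 6 months post enrolment".
- **Procedure** (the text after Figure 1) dates the follow-up surveys from a different origin: "3 and 6 months (91 and 183 days) post-randomization with a further two reminder emails at 7 day intervals if required". Anyone still silent after that is chased by phone. No date is given for the calls and no closing date for the survey.
- **Procedure** (opening paragraph) gives the order of entry. Participants click a "box for each element of the consent form in order to enroll in the study", verify an e-mail address and set up an account. Next comes: "Participants will then be directed to an online baseline survey before being randomized to study groups".

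Under Measures, "Both the primary and secondary outcome measures will be assessed at baseline, 3 and 6 month". Under Analysis, the effect is judged by the time-by-group interaction in an intention-to-treat MMRM, so the 6-month wave is part of the primary test. The last sentence of the Background uses a third origin for the same follow-up, counting 3 and 6 months from the intervention.

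**The concern.** In a wait-list design, the last control measurement should come before the control arm is offered the intervention. Here the stated access rule depends only on elapsed time, and it comes due at about the moment when 6-month data collection begins. Collection then continues for at least two weeks. A control who answers during the reminder or telephone stage can already have the modules available.

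The intervention is short. The Abstract puts all three modules at about 90 minutes, and the Procedure advises a week between modules but lets participants go at their own pace. A few days of access can therefore cover all of the content.

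If the intervention works, controls who have used it move towards the intervention arm and the 6-month difference shrinks. The ASSIST score is partly protected because most of its items look back over 3 months. Readiness to change, help-seeking intention and psychological distress are closer to current state, and the modules aim directly at motivation, so these secondary outcomes are more exposed. The exposure cannot be undone once the data are collected.

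**Working it through.** **Inputs**

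- Access: 6 months after enrolment (Design).
- Invitation: day 183 after randomization (Procedure).
- Reminders: two, 7 days apart (Procedure).
- ASSIST look-back: last 3 months (Measures), taken as 91 days, which is the article's own conversion of 3 months.
- Gap from enrolment to randomization, *g*: not stated. The main case uses *g* = 0; values of 7 and 14 days are assumptions.

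**Step 1. Reproduce the article's figure.** 6 × 365.25 / 12 = 182.6, which rounds to the stated 183 days.

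**Step 2. Collection dates.** First reminder: 183 + 7 = day 190. Second reminder: 190 + 7 = day 197. Calls come after that, undated.

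**Step 3. Lead time of access.** On the randomization clock, access opens at day *M* − *g*, where *M* is 6 months in days. Lead = response day − (*M* − *g*).

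| Case | At invitation (183) | At reminder 1 (190) | At reminder 2 (197) |
|---|---|---|---|
| *M* = 183, *g* = 0 | 0 days | 7 days | 14 days |
| *M* = 184 (longest half-year), *g* = 0 | −1 day | 6 days | 13 days |
| *M* = 181 (shortest half-year), *g* = 0 | 2 days | 9 days | 16 days |
| *M* = 183, *g* = 7 (assumed) | 7 days | 14 days | 21 days |
| *M* = 183, *g* = 14 (assumed) | 14 days | 21 days | 28 days |

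In every row, access is open before both reminders. Access before the invitation needs either a gap or a short calendar half-year.

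**Step 4. Share of the look-back.** 7/91 = 8%; 14/91 = 15%. Under the assumed gaps, 21/91 = 23% and 28/91 = 31%. These are upper limits on time with access. They do not measure use of the modules or bias.

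**Step 5. Rough scale for power (illustration only).** Assumptions: *f* = .27 read as *d* = 2 × .27 = 0.54, two-sided alpha 0.05, 80 × 0.8 = 64 completers per arm, and a simple two-group comparison at one time point. Power ≈ Φ(*d*√(n/2) − 1.96).

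- No exposure: 0.54 × √32 − 1.96 = 1.095, so power is 0.86.
- 20% of controls exposed, each gaining 15% of the effect (in proportion to the look-back): *d* = 0.54 × (1 − 0.20 × 0.154) = 0.523, so power is 0.84.
- 10% or 20% of controls exposed, each gaining half of the effect: *d* = 0.513 or 0.486, so power is 0.83 or 0.79.

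The shares and gains are assumed. The second line is nearer to what the ASSIST look-back suggests. The third is a less favourable case, of the kind that a current-state measure could show.

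**The case against.** The strongest reply is that this is a condensed article. Figure 1, which the Procedure cites for participant flow, is not available here, and either it or the full protocol may open the survey before the modules. The usual understanding of a wait-list is also assessment first, then access. This could well be the intention. However, the article does state a rule, and that rule is a calendar date which overlaps the stated collection period. If the flow is already ordered correctly, the Design sentence still needs correcting.

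A second reply concerns the gap. Consent is a condition of enrolling and need not be the enrolment date, and the Discussion pairs randomization with entry into the study. On that reading *g* is zero. This stands, and the conclusion therefore rests on the zero-gap row.

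A third reply is about scale. The exposure needs controls who leave a paid survey (AU$20) unanswered through the invitation and a reminder, yet work through the modules. There may be few of them. The look-back dilutes any change, and two ASSIST topics (concern from others and failed attempts at control) are asked as ever having happened. This stands too, and it keeps the expected effect on the primary outcome small.

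A reader might infer that access precedes the survey for all controls, or that the control arm is contaminated at 6 months. The documents do not support either. They leave exposure possible for late responders and give no figure for how many there would be. A reader might also conclude that control responses given after access should be left out of the primary analysis. That would remove observed outcomes from one arm on the basis of behaviour after randomization, against the intention-to-treat MMRM, and could create informative missingness on one side.

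**Conclusion.** The point holds as a possibility that the stated timing rules leave open. With no enrolment gap, controls answering at the first or second reminder can have had about 7 or 14 days of access, the latter being 15% of the ASSIST look-back. Figures of 21 or 28 days rest on assumed gaps or call dates. The 3-month wave is untouched. At 6 months the likely effect on the primary outcome is small and mainly towards no difference, with more exposure for readiness to change, help-seeking intention and distress. The conclusion assumes that the access rule is applied as worded and that Figure 1 or the full protocol does not already place the survey first. The change is worth making because the problem is easy to prevent and cannot be repaired afterwards.

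**What to change.** 1. Reconcile Design and Procedure on one clock, randomization, and align the follow-up origin given in the Background with it.
2. State that control access opens only once the participant's 6-month survey is completed or, for non-responders, once a fixed survey window that includes the telephone stage has closed.
3. Record each control participant's first-access date.
4. Keep all observed responses in the intention-to-treat MMRM. If any control response follows access, exclude it only in a sensitivity analysis.

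The cost is one condition in a program that already automates randomization and releases modules in sequence, plus a sentence or two of text. According to the Status section, recruitment had not begun. There are two small downsides: non-responding controls wait until the window closes, and controls gain a slight extra incentive to respond, which could make follow-up differ a little between arms. Opening access to everyone when the window closes limits both. If Figure 1 or the full protocol already orders the steps this way, only the wording needs to change.

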### Sample

Participants will be recruited via a variety of sources: youth magazines, web-sites, social networking sites, universities and clinics. The inclusion criteria are: resident in Australia, aged 18 years or older and use of amphetamine type stimulants (e.g. meth/amphetamine, ecstasy, non-medical use of prescription stimulants) in the last 3 months. Furthermore, participants need to have access to the internet, a valid e-mail address, telephone access and to provide informed consent. The exclusion criteria are: currently receiving any treatment for stimulant abuse/dependence, currently receiving pharmacotherapy for any substance use disorder (e.g. methadone, naltrexone, buprenorphine) except nicotine replacement therapy; self-reported lifetime diagnosis with schizophrenia, schizoaffective, or bipolar disorder.

### Procedure

Enrolment and screening will be undertaken via the internet. Advertisements will direct participants to the study web address. First, participants who visit the study website will be given information on the project and their eligibility assessed by means of a series of online questions. Based on their answers, participants who are not eligible for the study will be given information about other potentially useful websites and resources (e.g. mental health, alcohol or other drugs websites and helplines). Participants who are eligible for inclusion will be asked to provide active consent by ‘clicking’ on a box for each element of the consent form in order to enroll in the study. Figure1 illustrates the flow of participants through the study. Participants will be asked to provide an e-mail address that will be verified via a personalized link in an automated email. This link will take participants to the study site where they will set their own username and password. Participants will then be directed to an online baseline survey before being randomized to study groups. The randomization process will be fully automated with permuted blocks of four and will be implemented within the program.

**Figure 1 F1:**
[figure not shown]
Participant flow through the study.

Participants who are assigned to the intervention group will then be provided with immediate access to the first module of the intervention. These participants will be advised to allow 1 week between modules, but are allowed to proceed at their own pace. Participants must visit each page of a module in sequence to complete the module and thus obtain access to the next one. The intervention group will receive emails at seven day intervals after the commencement of the trial period, either asking them to start the next module, if they have not already commenced that module, or inviting them to revisit the site. A further e-mail will be sent to those who do not start the current module at 3 days after the module was scheduled for commencement. Participants will be invited via e-mail to complete follow-up assessment at 3 and 6 months (91 and 183 days) post-randomization with a further two reminder emails at 7 day intervals if required, followed by a telephone call(s) for participants who do not respond to the emails. Participants will receive AU$20 for baseline assessment and for each follow-up questionnaire that they complete, paid as either on-line vouchers or posted cheques.

The Australian National University Human Research Ethics committee approved the study, which is also registered with the Australian and New Zealand Clinical Trials Registry (www.anzctr.org.au/) ACTRN12611000947909.

